**Figure 2 F2:**
[figure not shown]
Ten postures of Baduanjin exercise.

#### Control group

The control group will perform exercises based on basic western medicine treatment and health education. During hospitalization, we will conduct supervisory training for the control group to ensure that patients exercise 3–5 times a week (such as walking). After discharge, there will also be special researchers to supervise through Wechat or the phone. The main form of exercise is moderate-intensity free exercise, lasting 8 weeks, for 3–5 times a week.

#### Concomitant treatment

All patients will receive routine treatment, such as aspirin, clopidogrel, statins, ß-receptor blocker, and angiotensin-converting enzyme inhibitors. Drug changes of all patients will be recorded in the comprehensive drug record sheet.

### Sample size

The sample size was calculated according to the effective rate of the Baduanjin group and the control group. Referring to the previous research (27), it is assumed that the effective rate of the combination of traditional Chinese medicine and western medicine is 76.2%, and the effective rate of western medicine is 45.8%. Based on the class I error rate of α = 0.05 and the efficacy of 90% (II error rate of β = 0.1), bilateral test, and considering the shedding of 20%, the experiment was expanded to 69 people. Because the reference study is drug intervention, considering that this study is non-drug intervention, we continue to expand the sample size to 90 people in each group, a total of 180 people.

$$\begin{array}{l} n=\frac{{\left(u_{\alpha }+u_{\beta }\right)}^{2}\left(1+1/k\right)p\left(1-p\right)}{{\left(p_{e-}p_{c}\right)}^{2}} \end{array}$$

### Outcome measurements

Table 1 provides a detailed overview of the items that will be measured for the primary and secondary results, and the time of data collection. The main outcome indicators will be measured prior to the experiment (week 0), after the end of the trial (week 8), and at 3 and 6 months after enrollment. Data on the secondary outcome indicators, including the duration of angina pectoris, number of angina pectoris weeks, nitroglycerin consumption, nitroglycerin reduction rate, SAQ, quality of life (SF-36), and TCM syndrome scores, will be collected at weeks 0, 4, and 8 and months 3 and 6. Details on secondary outcome indicators, including electrocardiogram (ECG) readings, blood lipid and hs-CRP levels, and intestinal microflora, will be collected during weeks 0 and 8. All measured outcomes will be recorded in the case report form.

**Table 1 T1:** Schedule of trial measurements for primary and secondary outcomes.

**Study phase**		**Screen/enroll**	**Allocation**	**Intervention period**	**Intervention end**	**Follow-up period**	**Follow-up period**
**Time points**		**Week 0**		**Week 4**		**Month 3**	**Month 6**
Screening/enrollment	Eligibility screening	•	•	—	—	—	—
	Informed consent	•	—	—	—	—	—
	Baseline measurement	•	—	—	—	—	—
	Random allocation	—	•	—	—	—	—
Intervention	Baduanjin exercise	—	•				•
	Free activities	—	•				•
Outcome assessment	Total effective rate	—	•	•	•	•	•
	Duration	—	•	•	•	•	•
	Attack frequency	—	•	•	•	•	•
	Dosage	—	•	•	•	•	•
	Stopping rate of nitroglycerin	—	•	•	•	•	•
	SAQ	—	•	•	•	•	•
	SF-36	—	•	•	•	•	•
	ECG	—	•	—	•	—	—
	Serum lipids	—	•	—	•	—	—
	Hs-CRP	—	•	—	•	—	—
	The TCM syndrome scores	—	•	•	•	•	•
	Composition of gut microbiota	—	•	—	•	—	—
	TMAO	—	•	—	•	—	—
Safety index	—	—	•	—	•	—	—
Adverse events	—	—	•				•

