## Materials and methods

### Design

This single-center, randomized controlled trial will be conducted in Guang'anmen Hospital of China Academy of Chinese Medical Sciences. After providing written informed consent, 180 participants will be randomly assigned to the medium-intensity Baduanjin or medium-intensity control groups (free activities). Medium-intensity is defined as energy consumption (calories) per unit time, which is 3 to 6 times higher than that during meditation. The intervention time will be 8 weeks, followed by 6 months of follow-up, and the results will be evaluated immediately at the end of the follow-up period. Figure 1 illustrates the flow of this experiment; the scheme of the clinical trial is in line with the standard program project: intervention trial guidelines recommend (24) and follow the comprehensive standards for reporting trials (25).

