### Intervention

#### Baduanjin group

The Baduanjin group participants will focus on practicing at the Guang'anmen Hospital. During hospitalization, researchers guided and supervised the exercise, and after discharge, special researchers will supervise telephonically or through WeChat. Based on basic Western medicine treatment and health education, patients will perform eight stages of brocade exercise. Each exercise lasts about 30 min, including 5 min of warm-up exercise, 20 min of Baduanjin exercise, and 5 min of relaxation activities, lasting for 8 weeks, 3–5 times a week. The training program was formulated according to the “Baduanjin of Fitness Qigong,” issued by the State Administration of Sports in 2003, with a total of 10 postures (Figure 2). Participants should not be exercising extra.

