#### Primary outcome

The main outcome index is the total effective rate of angina pectoris symptoms, described in detail in Tables 2, 3. Data will be collected at baseline, weeks 4 and 8, and months 3 and 6 after enrollment.

**Table 2 T2:** Angina pectoris symptom scoring standard.

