### Data collection and management

If participants deviate from the intervention program, additional participants will be included to minimize data loss during the study period. Patients will be supervised and guided by specialized researchers throughout the intervention. At the fourth and eighth weeks, participants will be required to return to the hospital for scale (Such as clinical symptoms, SAQ and TCM syndrome scores) or clinical-related tests, and regular telephonic follow-up will be conducted by researchers during the follow-up period. Researchers remind patients to undergo daily moderate-intensity training, and those who deviate from the intervention plan will receive telephonic reminders, to ensure the integrity of the study data.

Basic patient information and relevant information required for the study will be recorded in the printed case report form (p-CRF). The patient's medical records (medical records, test sheets, etc.) will be stored in the hospital, and the doctor records the patient's test results in the observation medical records. Only authorized researchers, ethics committee members, and relevant research management department members will be able to access patient records following reasonable request. The name and identity of the patient will not appear in the study and published papers. The research team will do everything possible to protect the privacy of patients' personal medical data from disclosure within the scope permitted by law.

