### Statistical analysis

A full-analysis set (FAS), per-protocol analysis set (PPS), and safety analysis set (SAS) will be created according to the principle of intentional therapy (34). FAS participants are identified as those who received at least one exercise. Those who adhere to the treatment plan but changed groups midway are part of the PPS. For safety indicator assessment, researchers will use the SAS to analyze the incidence of adverse events and laboratory indicators. Statistical analysis will be conducted by third-party statisticians blinded to experimental grouping and intervention methods, using SPSS 25. We will analyze the baseline demographic data to determine the comparability between the two groups. Mean ± standard deviation will be used for continuous variables that conform to normal distribution, and median and quartile methods will be used for continuous variables that do not conform to normal distribution. The Chi-square test or Fisher's exact test will be used to compare classified counting data. The paired *t*-test will be used to compare differences within the group, and the independent-sample *t*-test will be used to compare differences between groups. If the data do not conform to normal distribution, a Wilcoxon paired test and Mann-Whitney U test will be used to analyze intra- or inter-group differences. *P* < 0.05 is considered as statistically significant.

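### The primary outcome has conflicting visit schedules and no named primary time, which leaves open a choice among three or four comparisons at P < 0.05

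*Protocol article*

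**What the plan says.** **Timing of the primary outcome.** The Outcome measurements section states "The main outcome indicators will be measured prior to the experiment (week 0), after the end of the trial (week 8" and continues with 3 and 6 months after enrollment, which gives three post-baseline times. The Primary outcome section states "Data will be collected at baseline, weeks 4 and 8, and months 3 and 6 after enrollment", which gives four. Table 1 agrees with the second version: its total effective rate row is marked at week 4, intervention end, month 3 and month 6. The Design section says that "the results will be evaluated immediately at the end of the follow-up period".

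**Definition.** The note under Table 3 computes the efficacy index from a pre-trial and a post-trial symptom score and gives no week or month for the latter.

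**Testing.** The Sample size section plans one comparison of two rates: "Based on the class I error rate of α = 0.05 and the efficacy of 90% (II error rate of β = 0.1), bilateral test". Statistical analysis names the chi-square or Fisher's exact test for categorical data and a significance threshold of P below 0.05. Neither section names a time point.

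**Clock and exercise.** Design says "The intervention time will be 8 weeks, followed by 6 months of follow-up", whereas Outcome measurements and Primary outcome count months 3 and 6 from enrollment. The Baduanjin group section describes exercise "lasting for 8 weeks, 3–5 times a week"; Data collection and management says "Researchers remind patients to undergo daily moderate-intensity training".

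**The concern.** A responder at week 8 and a responder at month 6 are different endpoints. When a plan lists several times for one primary outcome, names none as decisive and applies a single unadjusted threshold, the time that favours the intervention can be chosen after the results are known. The 5% error rate used to size the trial then no longer describes the primary claim.

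This goes beyond a detail that an article leaves to the analysis plan. The article does address the timing and gives answers that disagree. A later analysis plan could adopt any of them and still say that it followed the protocol.

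**Working it through.** **1. Passages side by side (post-baseline times of the primary outcome)**

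- Outcome measurements, prose: week 8, months 3 and 6 (three times).
- Primary outcome section and Table 1: weeks 4 and 8, months 3 and 6 (four times).
- Table 3 note: post-trial, undated.
- Design: evaluation at the end of follow-up, with no reference to the primary outcome in particular.

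The phrase in Outcome measurements that equates the end of the trial with week 8, read together with the post-trial label under Table 3, leans toward week 8. No sentence says so.

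**2. The plan's own figure**

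Inputs from Sample size: rates 0.762 and 0.458, two-sided α = 0.05, power 90%, dropout 20%. With k = 1 and p = (0.762 + 0.458)/2 = 0.61:

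n = (1.960 + 1.282)² × 2 × 0.61 × 0.39 / 0.304² = 54.1, rounded up to 55 per group. Then 55/0.80 = 68.75, so 69. This matches the stated 69, and the formula covers one test at one time. The size of the trial is not at fault.

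**3. Chance of at least one false significant result**

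Assume no true effect, a two-sided test at 0.05 at each of m times, and that any one may carry the claim. With independent tests the chance is 1 − 0.95^m: 14.3% for m = 3 and 18.5% for m = 4. Visits on the same patients are correlated. The documents give no correlation, so a range is assumed. Simulation of equally correlated normal statistics (1,000,000 draws) gives:

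| Assumed correlation | Three times, either direction | Four times, either direction | Three times, one direction | Four times, one direction |
|---|---|---|---|---|
| 0.3 | 13.6% | 17.4% | 6.8% | 8.7% |
| 0.5 | 12.5% | 15.6% | 6.2% | 7.8% |
| 0.7 | 10.9% | 13.1% | 5.5% | 6.5% |
| 0.9 | 8.4% | 9.3% | 4.2% | 4.7% |

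The nominal levels are 5% in either direction and 2.5% in one. A cross-check simulated binary outcomes with 90 per arm, a common rate of 0.458 and latent correlation from 0.3 to 0.9. It gave 13.1% down to 9.8% for three times and 17.1% down to 11.7% for four.

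**4. Power once one time is named**

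Power = Φ[(0.304 − z × SE0)/SE1], where SE0 = √(2 × 0.61 × 0.39/n) and SE1 = √((0.762 × 0.238 + 0.458 × 0.542)/n). With n = 90 × 0.80 = 72 and z = 1.960: SE0 = 0.0813, SE1 = 0.0772, and power is about 97%. With n = 90 it is 99%. A Bonferroni split over four times (0.05/4 = 0.0125 each) would leave 90.4% power at each time with 72 per arm.

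**5. Follow-up clock**

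Six months is about 26 weeks. Counted from enrollment, the last visit falls at about week 26, or 26 − 8 = 18 weeks after an 8-week intervention. Eight weeks followed by six months puts it at about week 34. The two readings differ by about 8 weeks.

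**The case against.** The strongest reply is that the article says the outcome is measured and data are collected at these times. It does not say that each time will be tested, nor that any one would suffice. A multiplicity rule may sit in an analysis plan that is not shown. This stands: a reader might infer that the plan tests the primary outcome at every visit and so has a false-positive rate of 13–17%, but the documents do not support that. The figure needs four tests, a correlation of 0.3 to 0.7 that appears nowhere in the article, and a count of differences in either direction.

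It is also fair to say that the article leans toward week 8, and that the Design sentence may describe only when the evaluation is carried out. It is weak evidence for a rival primary time.

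A further tempting reading is that Table 1 carries exercise through to month 6, so that the later visits cannot show persistence of effect. The exercise rows show a mark, blank cells and a mark, as the adverse-events row does. That pattern may be a lost arrow or a merged cell, and the prose consistently describes an 8-week intervention. The table therefore does not establish the point. The daily-training sentence conflicts with the stated frequency but does not say that exercise continues after week 8.

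What the reply does not remove is the disagreement over week 4, the undated score in the endpoint definition and the lack of any named primary time.

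**Conclusion.** The concern holds as a risk that the text leaves open. The primary schedule is contradictory, no time is designated, and one unadjusted threshold applies. If any listed time could carry the claim, the two-sided chance of a false significant result is about 8–14% with three times and 9–17% with four, against the planned 5%. In Baduanjin's favour alone it is about 4–7% and 5–9%, against 2.5%. These ranges rest on an assumed between-visit correlation of 0.9 down to 0.3 and on unrestricted choice of time. They are not estimates of what the sponsor intends to do.

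The conflicts over the follow-up clock and exercise frequency are real but secondary. They blur what the later visits mean and have no part in the error calculation.

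**What to change.** Before any comparative data are seen:

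- Define the primary endpoint as the total effective rate at week 8, compared once at two-sided 0.05. Week 8 is the end of the planned intervention, an on-site visit, and the time of the ECG, blood and stool measurements.
- State under Table 3 that the post-trial score is the week 8 score for the primary analysis.
- Make months 3 and 6, and week 4 if it is collected, secondary. Align Outcome measurements, Primary outcome and Table 1.
- Reconcile the follow-up clock in Design and the abstract's Participants paragraph with Outcome measurements and Primary outcome.
- Reconcile the exercise frequency in Data collection and management with the abstract's Interventions paragraph and the two group descriptions. Which wording is right is for the sponsor to settle.

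**Cost.** No additional patients are needed: power is about 97% with 72 evaluable per arm under the plan's own rates. Trial status reports that recruitment has started, so this should be a dated and documented amendment, not a silent correction. The sponsor gives up the option of claiming primary success at another time.

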#### Primary outcome

The main outcome index is the total effective rate of angina pectoris symptoms, described in detail in Tables 2, 3. Data will be collected at baseline, weeks 4 and 8, and months 3 and 6 after enrollment.

**Table 2 T2:** Angina pectoris symptom scoring standard.

**Angina pectoris symptom scoring standard**			
**Number of seizures**		**Symptom**	**Integral**
	None	No attack within a week	0 point
	Mild	Attack 2–6 times a week	2 point
	Moderate	Attack 1–3 times a week	4 point
	Severe	Attacks more than 4 times a week	6 point
The degree of pain	None	No attack within a week	0 point
	Mild	Heavier than daily activities of physical activity caused angina pectoris	2 point
	Moderate	Daily physical activities cause angina pectoris, and daily activities are restricted.	4 point
	Severe	Physical activities that are lighter than daily activities cause angina pectoris, and daily activities are obviously limited.	6 point
The duration of the pain	None	No attack within a week	0 point
	Mild	The pain lasts ≤5 min	2 point
	Moderate	5 min < The pain lasts <10 min	4 point
	Severe	The pain lasts ≥10 min	6 point
Dosage of nitroglycerin	None	None	0 point
	Mild	Take 1–4 tablets a week	2 point
	Moderate	Take 5–9 tablets a week	4 point
	Severe	Take more than 10 tablets a week	6 point
		Total	____point

**Table 3 T3:** Evaluation of curative effect on angina pectoris symptoms.

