**Evaluation of curative effect on angina pectoris symptoms**	
Significant effect	Disappearance of symptoms or almost disappearance of angina pectoris symptom efficacy index ≥70%.
Effective	The frequency, degree and duration of pain attacks were significantly reduced by 30% ≤ angina pectoris symptom index <70%.
Invalid	The symptoms are the same as those before treatment. 0 ≤angina pectoris symptom efficacy index <30%.
Aggravate	The frequency, degree and duration of pain attacks were aggravated, the score of angina pectoris was increased, and the curative effect index of angina pectoris symptoms was <0.

Description: angina symptom efficacy index = (pre-trial angina symptom score-post-trial angina symptom score)/pre-trial angina symptom score × 100%. The symptom score of angina pectoris is the sum of the scores in Table 2. Total effective rate = (significant effect + effective)/sample size × 100%.

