#### Secondary outcome

(1) Clinical symptoms: after confirming that the patients meet the inclusion criteria, researchers will ask about and record the clinical symptoms of the patients (including the duration of angina pectoris, frequency of weekly attacks, and the dosage of nitroglycerin) at baseline, weeks 4 and 8, and months 3 and 6 after enrollment.(2) Stopping rate of nitroglycerin: This will be recorded at the baseline and at weeks 4 and 8 and months 3 and 6 after enrollment.① Significant effect: discontinuation of nitroglycerin after treatment;② Effective: the dosage of nitroglycerin after treatment is >50% less than that before treatment;③ Ineffective: after treatment, the dosage of nitroglycerin decreased by <50% or increased, compared with that before treatment.(3) SAQ: This is a 19-item self-administered questionnaire measuring five dimensions of coronary artery disease: physical limitation (question 1), anginal stability (question 2), anginal frequency (question 3–4), treatment satisfaction (question 5–8), and disease perception (question 9–11) (28). The 19 items will be scored individually to obtain the total SAQ score, which is transformed into a standard score according to this formula: Standard score = (actual score – lowest score of the dimension) x100/(highest score of the dimension – lowest score of the dimension). Patients' quality of life and body function are proportional to the score, which will be recorded at the baseline and weeks 4 and 8 and months 3 and 6 after enrollment.(4) SF-36: The MOS item short will be used from the health survey (SF-36) to assess patients' quality of life. As a concise health questionnaire, SF-36 comprehensively summarizes the quality of life of the subjects from eight aspects: Physical Functioning (PF), Role-Physical (PR), Bodily Pain (BP), General Health (GH), Vitality (VT), Social Functioning (SF), Role-Emotional (RE), and Mental Health (MH). There are 36 questions, and the quality of life is proportional to the score (29). SF-36 is effective in detecting the health perception of the general population, easy to use, and highly accepted by patients, and studies have proven it to be a promising tool due to its high reliability (30, 31). SF-36 will be recorded at baseline, weeks 4 and 8, and months 3 and 6.

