$$\begin{array}{l} \begin{array}{c} \text{PF}=(\text{Actual score}-\;20)/40\times 100;\\ \text{PR}=(\text{Actual score }-4)/4/4\times 100\\ \beta \text{P}=(\text{Actual score}-2)/10\times 100;\\ \text{GH}=(\text{Actual score}-5)/20\times 100\\ \text{VT}=(\text{Actual score}-4)/20\times 100;\\ \text{SF}=(\text{Actual score}-2)/8\times 100\\ \text{R}\epsilon =(\text{Actual score}-3)/3\times 100;\\ \text{MH}=(\text{Actual score}-5)/25\times 100 \end{array} \end{array}$$

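### Table 2's attack-frequency bands overlap and invert mild and moderate, so primary responder status can be wrong even with consistent coding; exactly 10 nitroglycerin tablets has no score

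*Protocol article*

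**What the plan says.** **Primary outcome, Table 2.** Four items are each scored 0, 2, 4 or 6: number of attacks, degree of pain, duration of pain and nitroglycerin use. For number of attacks, no attack within a week scores 0. The other bands are:
- mild, 2 points: "Attack 2–6 times a week"
- moderate, 4 points: "Attack 1–3 times a week"
- severe, 6 points: "Attacks more than 4 times a week"

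The nitroglycerin bands are 1–4 tablets, 5–9 tablets, and then "Take more than 10 tablets a week".

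**Table 3 and its note.** The four items are summed, and "angina symptom efficacy index = (pre-trial angina symptom score-post-trial angina symptom score)/pre-trial angina symptom score × 100"%. An index of 70% or more is *Significant effect*, 30% to below 70% *Effective*, 0 to below 30% *Invalid*, and below 0 *Aggravate*. The total effective rate counts the first two classes. Each class also has a verbal description, and nothing says which prevails if description and index disagree.

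**Secondary outcome.** Item (1) has researchers record attack duration, weekly attack frequency and nitroglycerin dosage at baseline, weeks 4 and 8, and months 3 and 6. Item (4) says of the SF-36: "There are 36 questions, and the quality of life is proportional to the score". It then prints eight transformation formulas, among them PF = (actual score − 20)/40 × 100, PR = (actual score − 4)/4/4 × 100 and RE = (actual score − 3)/3 × 100.

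**The concern.** A severity score has to give each patient state one value, and that value should not fall as the state gets worse. The printed frequency item fails on both counts: four attack counts have two admissible scores, and one attack a week scores higher than four. The summed score determines the efficacy index, and the index has fixed cut-offs, so an error of 2 or 4 points on one item can move a patient across the line between responder and non-responder in the primary outcome. The document prints this scoring key as the definition of the endpoint, so the matter is a contradiction in what is stated and not a detail left to an analysis plan. The article reports that recruitment has begun.

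**Working it through.** **1. The plan's own figure for this outcome.** Sample size section: effective rates 0.762 and 0.458, two-sided α = 0.05, power 90%, k = 1, pooled p = (0.762 + 0.458)/2 = 0.61. The printed formula gives n = 54.1, so 55 per group, and 55/0.8 = 68.75, so 69. This reproduces the stated 69, later raised to 90, and is not in dispute.

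**2. Points by attack count**, reading each printed band literally:

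| Attacks per week | Admissible points |
|---|---|
| 0 | 0 |
| 1 | 4 |
| 2 or 3 | 2 or 4 |
| 4 | 2 |
| 5 or 6 | 2 or 6 |
| 7 or more | 6 |

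**3. Wrong responder status with consistent coding.** The counts 1 and 4 each have a single score, so no choice is involved. Take attacks rising from 1 to 4, pain degree falling from 4 points to 2, duration 2 and nitroglycerin 0 throughout.
- As printed: before 4 + 4 + 2 + 0 = 10; after 2 + 2 + 2 + 0 = 6. Index (10 − 6)/10 = +40%, *Effective*.
- Under any increasing bands that keep 0 for no attack, let f₁ and f₄ be the points for 1 and 4 attacks, with 2 ≤ f₁ ≤ f₄. The index is (f₁ − f₄ + 2)/(f₁ + 6), which is at most 2/8 = 25%. The patient is never *Effective*.

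**4. A fall from 4 attacks to 1, other items unchanged.** As printed the item goes from 2 to 4. With the other items at 2 + 2 + 2 the total goes from 8 to 10, index −25%; with 2 + 2 + 0 it goes from 6 to 8, index −33.3%. Both are *Aggravate*. Under corrected bands:
- same band for 4 and 1: 0%, *Invalid*;
- one band apart: at most (8 − 6)/8 = 25%, *Invalid*;
- two bands apart: (12 − 8)/12 = 33.3% or (10 − 6)/10 = 40%, *Effective*.

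The label is wrong as printed, but the patient changes from non-responder to responder only in the last case.

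**5. A steady patient coded differently at two visits.** At 5 or 6 attacks, coded 6 then 2, the index is 4/(6 + s), where s is the sum of the other three items: 40% at s = 4, 33.3% at s = 6, 28.6% at s = 8. Only s = 4 or 6 reaches 30%, which is 4 of the 36 combinations of the other items (pain degree and duration each 2, 4 or 6; nitroglycerin 0, 2, 4 or 6). Coded 2 then 6, the index is negative in all 36. At a steady 2 or 3 attacks the most that can be gained is 2/8 = 25%, so no false response arises.

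**6. Scale of possible harm (illustration only).** The documents give no misclassification rate. Assume symmetric, non-differential misclassification of responder status and 90 × 0.8 = 72 evaluable per group at the design rates. Power is then 96.9% with none, 92.6% at 5%, 85.0% at 10%, 73.9% at 15% and 60.0% at 20%. At 10%, for example, the rates become 0.762 × 0.9 + 0.238 × 0.1 = 0.7096 and 0.458 × 0.9 + 0.542 × 0.1 = 0.4664.

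**7. SF-36 formulas.** The minima subtracted are 20 + 4 + 2 + 5 + 4 + 2 + 3 + 5 = 45. If every item is scored from 1 and enters one scale, the minima count the items and cannot exceed 36. The other seven use 25, leaving at most 11 for PF.
- PF: the printed range over minimum, 40/20 = 2, implies three-level items. With 11 such items the printed formula runs from (11 − 20)/40 × 100 = −22.5 to (33 − 20)/40 × 100 = 32.5; with 10 items, from −25 to 25.
- PR: if its four items are two-level, as the RE formula implies for RE, the best score is (8 − 4)/16 × 100 = 25. If they were five-level, it would be (20 − 4)/16 × 100 = 100 and the formula would be right.
- Both transformations are linear, so t-test P values do not change; the reported scores and differences do.

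**The case against.** **It may be a printing or translation slip.** The article cannot show that the working case report form carries these bands, and the source standard is not at hand. This stands as a limit on what is known. It does not remove the point, because this is the public definition of the primary endpoint and nothing in the article resolves the overlap.

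**The score is not backwards throughout.** A reader might infer that it is. Only mild and moderate are inverted; the severe band lies above moderate.

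**The obvious examples matter less than they seem.** A reader might infer that patients who improve from 4 attacks to 1 are lost as responders, or that unchanged patients readily become responders. Steps 4 and 5 do not support this. The first usually remains a non-responder after correction, since *Invalid* and *Aggravate* both count as failures. The second needs inconsistent coding at 5 or 6 attacks together with low scores elsewhere. The case that does carry the point is step 3.

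**Table 3's wording might rescue some patients.** In step 3 the frequency rises, which conflicts with the verbal description of *Effective*. But with no rule of precedence, the index is the only operational criterion.

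**Biased scoring is not established.** A reader might infer that unblinded scorers can pick the convenient score. The abstract's Design paragraph says outcome assessors were blinded, and the Discussion says allocation was confidential to evaluators. Randomization and blinding says that blinding researchers is not feasible and names only laboratory technicians and analysts as blinded. Until these are reconciled, what is shown is ambiguous scoring, not bias.

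**The SF-36 point is weaker.** It concerns a secondary outcome and rests on item-format assumptions. The formula block also prints Greek letters in place of Latin ones in BP and RE, so the repeated division by 4 could be a typesetting artefact. It justifies a check, no more.

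**Conclusion.** The point holds. As printed, the frequency item gives two admissible scores at 2, 3, 5 and 6 attacks a week and scores 1 attack above 4, and exactly 10 tablets falls in no band. Primary responder status can be wrong even when every rater follows the table consistently: +40% (*Effective*) in a patient for whom any increasing bands allow at most 25%. This rests on the printed tables and on keeping 0 points for no attack.

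The documents do not give the share of patients affected, and the power figures in step 6 are an illustration under a stated assumption. Whether the ambiguity also lets bias in depends on assessor blinding, on which the article contradicts itself. The gap at 10 tablets affects a single value and is minor. The SF-36 formulas need checking but carry little weight here: on the stated assumptions PF and PR would be reported off scale, with t-test P values unchanged.

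**What to change.** - Reconcile the attack-frequency bands with the source standard, including the time unit of each row, so that they are mutually exclusive, exhaustive and increasing. No cut-points are proposed here.
- Close the gap at exactly 10 tablets.
- State whether the index or the verbal description decides the class in Table 3.
- Correct the case report form, and re-score all enrolled patients blind to arm from the weekly attack and tablet counts. Secondary outcome item (1) has these recorded at every primary time point; this assumes they were entered as counts and not as bands.
- Reconcile the statements on assessor blinding.
- Check the PF and PR formulas against the SF-36 scoring manual, so that the lowest and highest raw scores map to 0 and 100.

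The cost is a protocol amendment, a form correction and one re-scoring from existing records. No extra patients or visits are needed, and the sample size is unaffected.
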